## Abstract

**Background:**

Depression in adolescents is a significant problem that impairs everyday functioning and increases the risk of severe mental health disorders in adulthood. Relatively few adolescents with depression are identified and referred for treatment indicating the need to investigate alternative preventive approaches.

**Study Design:**

A pragmatic cluster randomised controlled trial evaluating the effectiveness of a school based prevention programme on symptoms of depression in "high risk" adolescents (aged 12-16). The unit of allocation is year groups (n = 28) which are assigned to one of three conditions: an active intervention based upon cognitive behaviour therapy, attention control or treatment as usual. Assessments will be undertaken at screening, baseline, 6 months and 12 months. The primary outcome measure is change on the Short Mood and Feeling Questionnaire at 12 months. Secondary outcome measures will assess changes in negative thoughts, self esteem, anxiety, school connectedness, peer attachment, alcohol and substance misuse, bullying and self harm.

**Discussion:**

As of August 2010, all 28 year groups (n = 5023) had been recruited and the assigned interventions delivered. Final 12 month assessments are scheduled to be completed by March 2011.

**Trial Registration:**

ISRCTN19083628

## Background

Epidemiological studies suggest that over a six month period up to 8% of adolescents suffer from a major depressive disorder [1]. Cumulative rates indicate that up to 20% will experience at least one clinically depressive episode by the age of 18 [2]. Adolescent depression causes significant impairment, impacts on developmental trajectories, interferes with educational attainment, and increases the risk of attempted and completed suicide as well as major depressive disorder in adulthood [1,3-5]. In addition, sub-threshold depressive symptoms in adolescence carry a similar risk to major depression for developing depression and suicidal behaviours later in life [6]. Whilst approximately 50% of children are estimated to spontaneously recover, for the remaining half symptoms persist and significantly impair functioning [7]. It is therefore particularly concerning to note that depression in adolescents often remains unrecognised and untreated [8,9].

Reducing rates of adolescent depression is an important public health issue and has resulted in growing interest in the development of preventative interventions. A recent review identified almost 30 different depression prevention programmes which can be delivered in schools [10]. These are either provided universally to all young people irrespective of risk status or in more targeted ways, i.e. to adolescents at increased risk of developing depression or already demonstrating mild/moderate problems [11]. The inclusivity of universal programmes minimises negative effects of stigma and labelling, resulting in higher participation rates and lower rates of dropout [12-14]. In addition, universal programmes provide opportunities for primary prevention, i.e. reducing the onset of new problems, through the promotion of skills which develop good psychological health and resilience. However, from an economic perspective, interventions are provided for children who may not ever require them. Furthermore, in terms of effectiveness, targeted interventions typically result in greater reductions in depressive symptoms [2,10,15]. This may be due to initial levels of depressive symptoms in targeted groups being higher resulting in greater post intervention reductions [15]. Whilst universal approaches might have a more limited effect on individuals, they offer the potential to reduce far more disorders in the population as a whole than a highly effective targeted approach [16,17].

Despite the proliferation of school based depression prevention programmes, current research suffers from significant methodological limitations [2,10,15,18]. Studies are often underpowered, medium term follow-ups are lacking, and few have included comparisons with other active interventions. Most are efficacy studies assessing interventions under highly controlled conditions and no trials have been undertaken within the UK educational system. In terms of programme content, those based upon cognitive behaviour therapy (CBT) tend to show most promise. The majority of CBT based programmes produce immediate reductions in depression scores although these gains are not always maintained at follow-up. There are also considerable differences between programmes in the number of sessions, core components and delivery (e.g. delivered by teachers or health professionals). Variations in effectiveness within similar programmes suggest the importance of mediating and moderating factors.

One promising universal depression prevention programme is the Australian Resourceful Adolescent Programme (RAP). In the initial efficacy study, 260 adolescents were assigned to RAP, RAP plus family involvement or a no intervention group [19]. In terms of reach, 85% of the eligible cohort took part and attrition was low at 5.8%. Adolescents who received either version of RAP reported significantly lower levels of depressive symptomatology at post intervention and 10 month follow-up compared with the no intervention group.

In a New Zealand adaptation of the programme, RAP-Kiwi, 392 students were assigned to either RAP-Kiwi or an attention placebo condition [20]. Recruitment rates were again high (73%), attrition low (9% attrition at 6 months) and depression scores were significantly lower in the RAP group post intervention. The results were less clear at the 18 month follow-up where differences on one of the two depression scales were maintained.

Finally, a large multi-site randomised controlled effectiveness trial in Australia of RAP involving 2664 students from 12 schools has recently been undertaken [21]. RAP participants recorded significantly lower levels of depressive symptoms than those in the control condition at both post-intervention and 12-month follow-up. Based on initial depression scores, significantly more (49%) of the at-risk students in the RAP condition moved into the healthy category at post-intervention compared with the control group (35%). This difference was maintained at 12 month follow-up. In a subsequent qualitative evaluation with 109 young people, 61% of girls and 46% of boys were able to identify specific examples where they had used skills learned during RAP [21]. The authors concluded that within the context of a real world effectiveness study RAP appears to positively affect the health status of "at risk" students.

In conclusion, there is evidence to suggest that school based preventive approaches can have a short term effect upon adolescent depression. However, most trials are small underpowered efficacy studies which have rarely involved comparisons with other groups.

## Methods and design

### Aim of the study

The primary aim of this study is to examine whether a school based CBT programme (Resourceful Adolescent Programme) is more effective than an attention control or usual school curriculum in reducing depressive symptoms in "high risk" adolescents attending UK schools.

### Design

The study is a pragmatic cluster randomised controlled trial comparing the effectiveness of three school based interventions: CBT, attention control or usual school curriculum. The arms are summarised in Table 1.

**Table 1 T1:** Arms of the PROMISE Randomised Controlled Trial

Study Arm	Content	Delivery
Treatment as usual	Normal school curriculum	One school staff

Attention control	Normal school curriculum	One school staff (leading sessions) plus two facilitators

Cognitive Behaviour Therapy	Resourceful Adolescent Programme	Two facilitators (leading sessions) plus one school staff

Interventions are delivered in schools to whole classes of children as part of the school curriculum. Assessments are administered at initial screening, baseline (2 weeks after screening), 6 months and 12 months.

### Participants and Eligibility

Interventions are provided as part of the school personal, social and health education (PSHE) curriculum. All pupils in years 8-11 (12-16 years old) are eligible to participate. Children are ineligible if they are not attending school (e.g. long term sickness, excluded from school, educated elsewhere) or do not participate in PSHE for religious or other reasons.

### Ethical Approval and Consent

The study was approved by the School for Health Research Ethics Approval Panel at the University of Bath. Consent/assent involves three stages. Firstly, eligible schools were provided with information about the study and interested head teachers were required to provide written confirmation that their school wanted to participate. Secondly, information was posted to the parents of all eligible children at their home address. Parents were invited to return a form opting out of the study if they did not wish their child to complete the study assessments. Finally, children were provided with information about the study and were required to provide written assent before completing assessments if they decided to opt in. Dual carer/child consent/assent was required for assessment completion.

The ongoing conduct and progress of the trial is monitored by two independently chaired committees. The Data Monitoring and Ethics Committee (DMEC) and a Trial Steering Committee (TSC) meet at least annually.

### Recruitment

A list of 66 mixed non-denominational comprehensive secondary schools in five sites incorporating urban and rural areas (Nottingham, Nottinghamshire, Wiltshire, Bath and North East Somerset and Bristol) was complied from local authority information. Project information sheets were sent to the Head Teachers and PSHE leads at each school. Meetings were arranged with staff at those schools who expressed interested and participation required a signed letter from the head teacher.

Nine schools were recruited, one for the pilot study and 8 for the main trial. In the main trial, one is a new school and does not have a Year 11 group. A further two schools could not include their Year 11 groups and one of these was also unable to include their Year 10 group. In total, the 8 schools recruited for the main trial comprise 28 year groups, 222 classes, and involves 5,768 young people.

### Randomisation

Allocation of year groups was undertaken once all schools were recruited. Trial arms were balanced with respect to key characteristics by calculating an imbalance statistic for a large random sample of possible allocation sequences [22]. The variables used for balancing were school, available year groups, number of students, number of classes, PSHE frequency and timetabling of PSHE lessons. A statistician with no other involvement in the study randomly selected one sequence from a subset with the most desirable balance properties.

### Participant Classification

All young people in a year group receive the intervention to which the year group is assigned (i.e. universal delivery). However, the primary aim of the study is to determine the effects on adolescents identified as at "high risk" of depression. Classification of risk is based upon two criteria, i.e. raised levels of depressive symptoms and continuity over time. Research with clinical and community samples demonstrates that adolescents who fulfil diagnostic criteria for depression achieve mean scores on short forms of the MFQ in the range of 7.01 - 11.95 compared with 3.24 - 4.68 for those who are not depressed [23-26]. A score of 5 was chosen to categorise adolescents as either low (< 5) or high risk (≥ 5). To account for transient changes in mood, MFQ scores are collected on two separate occasions approximately two weeks apart. Adolescents, who display persistent symptoms, i.e. scoring ≥ 5 on both occasions, will form the high risk group and we predict that approximately 20% will fall within this category.

### Interventions

#### Resourceful Adolescent Programme (CBT)

The Resourceful Adolescent Programme (RAP) consists of 9 modules and 2 booster sessions, each lasting approximately 50-60 minutes. The modules can be flexibly delivered in order to fit within the school timetable. Each programme is led by two trained facilitators working alongside the class teacher.

RAP is based upon cognitive behavour therapy (CBT) but also draws upon ideas from interpersonal therapy and specifically targets low mood. Through the programme, young people are helped to recognise the importance of negative thoughts and low self-worth/image in the onset and maintenance of depression. Core components include psycho-education, identifying and challenging negative/dysfunctional thoughts, identifying personal strengths (thereby enhancing self-esteem/image), managing social problems, and learning to problem solve.

In the first session, young people are introduced to RAP and are helped to identify their existing strengths and personal resources, thereby emphasising the importance of developing and maintaining good self-esteem. Modules two and three are concerned with emotional recognition and management. Physiological symptoms associated with different emotional states are identified and young people are encouraged to practice and use a variety of strategies to manage any unpleasant feelings. The fourth and fifth modules focus upon cognitions and highlight helpful and unhelpful ways of thinking. Common negative ways of thinking (i.e. thinking traps) are identified and young people are provided with a framework for checking and reappraising their cognitions. Module six is concerned with problem solving and the development of a stepped approach to generate and evaluate possible solutions to challenges. The seventh module highlights the importance of support networks and who young people can approach to help them cope with problems. Modules eight and nine are concerned with conflict resolution and how helping to understand another person's perspective can lead to "win-win" solutions. Two additional booster sessions will be provided approximately 6 months later. These will provide opportunities to review all RAP skills and to practice applying them to a number of common difficulties.

### Attention Control

The attention control intervention involves similar time and contact as the CBT intervention. The class teacher leads and delivers their usual PSHE curriculum, but is joined by two facilitators who assist with delivering the lessons and engaging with young people. This controls for the non-specific effects of interventions that are considered important in studies of depression [27]. In the same way as RAP, the delivery of the Attention Placebo intervention is flexible to fit with the existing school PSHE programmes.

### Usual PSHE

Young people participate in the usual personal health and social education (PSHE) sessions provided by the school (i.e. treatment as usual). The sessions are provided solely by the teacher and do not involve any external input from the research team. The content of the usual PSHE sessions will be examined to determine any potential overlap with the active intervention.

### Facilitators

Two facilitators are provided for the RAP and attention control group. Facilitators have at least an undergraduate university degree (some also had postgraduate qualifications) in a relevant discipline. All have appropriate professional backgrounds, including experience of working with young people. Separate initial training and on-going supervision was provided for the facilitators in each group. Wherever possible, the two facilitators are scheduled to remain with their assigned classes for the duration of the intervention.

### Outcome Measures

#### Primary Outcome

The primary outcome measure is changes in the level of symptoms of low mood as determined by the Short Mood and Feelings Questionnaire (SMFQ) at 12 months after the start of the trial [23]. The SMFQ is a unifactorial scale with a robust single factor structure [28,29]. Criterion validity (i.e. ability to predict clinical diagnosis) has been established within both clinical [23] and community samples [25,30] and with children ranging in age from 7-16. The scale correlates well with other measures of depression, has good test/re-test reliability with higher scores tending to be associated with children who fulfil diagnostic criteria for clinical depression [23-25].

#### Secondary Outcomes

A range of secondary outcome measures are also being collected. Negative thoughts will be assessed by examining scores on the personal failure sub-scale of the Children's Automatic Thoughts Scale (CATS; [31]. The Rosenberg Self-Esteem Scale assesses changes in self-worth and self-acceptance [32]. The Revised Child Anxiety and Depression Scale (RCADS;[33] assesses changes in symptoms of DSM-defined anxiety disorders and major depression in children. Five sub-scales assess symptoms of generalised anxiety disorder, separation anxiety disorder, social phobia, panic disorder and major depressive disorder. The degree to which children feel accepted, valued respected and included in their school is assessed by the short form of the Psychological Sense of School Membership (PSSM) scale [34]. The relationship with friends is assessed by the Attachment Questionnaire for Children [35]. Finally, questions will assess the extent to which children have bullied others, been the victim of bullying; drunk alcohol; smoked cannabis; taken other drugs; experienced thoughts of self harm and whether they have harmed themselves.

### Economic Evaluation

Quality of Life is assessed by the EQ-5D. This is a standardised instrument to assess health outcomes and assesses 5 dimensions of health (mobility, self-care, usual activities, pain/discomfort anxiety/depression). Usage of health services is assessed via a modified (self completed) version of the Client Service Receipt Inventory [36] which measures the use of health, education and social care services over the previous 6 months.

Incremental cost-effectiveness analysis using the primary clinical outcome, (i.e. SMFQ) and cost-utility analysis (i.e. cost per QALY, on the basis of utility estimates derived from EQ-5D scores) for all included comparators over the 12-month time horizon of the trial will be undertaken. These analyses will be from a societal perspective, capturing and where possible valuing cost and other potential impacts of the intervention across the health, education and social care sectors. Sensitivity analysis will be used to express uncertainty in the cost-effectiveness estimates

### Power calculation

The pilot site (n = 711) provided estimates of ICC (0.025), mean year group size (n = 203) and consent rate (84%) and SMFQ standard deviation (4.9). Based on 80% consent, 80% retention and 20% of children being classified as "at risk", effect sizes in the range of 0.36-0.42 SDs are detectable with 80% power and 5% two-sided alpha with 20-27 year groups. These are equivalent to differences in SMFQ scores of around 2 points. A total of 28 year group groups have been randomised.

### Statistical analysis

Data analysis will be undertaken blinded to allocation. The quantitative data will be analysed and the study reported in accordance with the CONSORT guidelines for randomised controlled trials [37]. Using routine data, we will compare characteristics of participating schools with (a) schools that were invited and did not participate, (b) schools in England. Within the eight schools, we will also compare characteristics of participating students with those who did not take part in any PSHE sessions, and those who did not provide consent to complete study questionnaires. Using appropriate descriptive statistics, we will assess comparability of the three trial arms at baseline, and to describe the number and characteristics of participants who do not provide outcome date at follow up.

The primary outcome is the Short Mood and Feelings Questionnaire (SMFQ) 12 months after baseline. The primary analysis will be restricted to participants identified as 'high risk' based on their screening and baseline SMFQ scores (≥ 5 on both occasions).

The first stages will involve examination of the distribution of SMFQ 12-month scores. Scores for each of the trial arms will be described using mean (SD) or median (IQR) as appropriate and appropriate transformation of the data undertaken if required. The primary intention-to-treat (ITT) analysis will be an analysis of covariance that takes appropriate account of the clustered design and school structure, implemented using random effects linear regression models in MLwiN software. Depending on extent of missing primary outcome data, the primary analysis will be repeated using complete data set generated using multiple imputation. The two comparisons of primary interest are the RAP arm versus each of the two control arms, presented as between-group differences in means, 95% confidence intervals and p-values adjusted for multiple comparisons using Dunnett's correction. Covariates in the model will comprise SMFQ baseline score and the six variables used to balance the trial arms in the allocation procedure.

Although year group is the unit of allocation, PSHE sessions are delivered to classes nested within year group, and year groups are themselves nested within schools. We will therefore investigate the components of variance at individual, class, year group, and school level before determining the final model which will be at least a two-level model (individual + year group), and may be up to a four-level model.

Analysis of secondary outcomes will be undertaken using the same general approach as for the primary analysis, using linear or logistic regression models for continuous or binary outcomes as appropriate. As a pragmatic trial of intervention 'effectiveness' (rather than 'efficacy'), the primary ITT analysis makes no attempt to take account of actual intervention received. We will also investigate efficacy among participants who comply with the intervention using instrumental variable methods [38]. Finally, using appropriate interaction terms in regression models, we will undertake subgroup analyses of SMFQ continuous score at 12 months according to baseline (i) SMFQ (< 5, 5-10, ≥ 11), (ii) self-harm, (iii) alcohol/drug misuse, (iv)year group, (v) Family Affluence Scale

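### The primary model rests on 28 year groups and adjusts for six mostly cluster-level variables, but its Dunnett tests are not tied to between-year-group degrees of freedom; z-based tests would exceed the 5% error rate

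*Protocol article*

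**What the plan says.** All references are to the protocol article.

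- **Number of units.** Power calculation: "A total of 28 year group groups have been randomised". Recruitment places them in 8 schools. The year group is the unit of allocation, and there are three arms.
- **Model.** Statistical analysis: an analysis of covariance "implemented using random effects linear regression models in MLwiN software".
- **Covariates.** "Covariates in the model will comprise SMFQ baseline score and the six variables used to balance the trial arms in the allocation procedure". Randomisation lists them: "The variables used for balancing were school, available year groups, number of students, number of classes, PSHE frequency and timetabling of PSHE lessons". Their coding is not given.
- **Comparisons.** RAP against each of the two control arms, with Dunnett-corrected p-values and 95% confidence intervals.
- **Levels.** Two to four, settled after the variance components have been examined. Individual and year group are always included.

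The article does not state the estimator, the reference distribution, the degrees of freedom or a small-sample correction.

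**The concern.** Arms were allocated to year groups, so the treatment contrasts carry at most the information of 28 units. The balancing variables describe year groups or schools, so they use up degrees of freedom at that same level, not among the pupils. After the three arm means and these covariates, few degrees of freedom remain for estimating the variance that the contrasts are judged against.

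Two things can then go wrong. A normal critical value ignores the uncertainty in that variance. ML also makes no allowance for the fitted cluster-level parameters, so it estimates the year-group variance too low and often at zero. A Dunnett adjustment applied to the resulting z statistics carries the error forward. The chance of wrongly declaring RAP different from a control would then exceed the nominal 5%, and the intervals for both primary comparisons would be too short.

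**Working it through.** **Inputs (Power calculation section).** "The pilot site (n = 711) provided estimates of ICC (0.025), mean year group size (n = 203"); "SMFQ standard deviation (4.9"); "Based on 80% consent, 80% retention and 20% of children being classified as" at risk.

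**1. Analysed pupils per year group.** m = 203 × 0.80 × 0.80 × 0.20 = 25.98, about 26. Design effect = 1 + 24.98 × 0.025 = 1.625.

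**2. The plan's own figure.** The stated result is "effect sizes in the range of 0.36-0.42 SDs are detectable with 80% power and 5% two-sided alpha with 20-27 year groups". With k year groups in three equal arms, the effective n per arm is (k/3) × 25.98 / 1.625, and the detectable effect is (critical value + 0.842) × √(2 / effective n). With the large-sample Dunnett value for two comparisons, 2.212:
- k = 27: 3.054 × 0.1179 = 0.360 SD
- k = 20: 3.054 × 0.1370 = 0.418 SD

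This reproduces 0.36-0.42. Dunnett with t on k − 3 df gives 0.379-0.450, which does not. An unadjusted t calculation on 2k/3 − 2 df comes close (0.352-0.420), so the match does not settle which method was used.

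**3. Degrees of freedom left.** Coding is assumed:
- School as 7 dummies, year as 3, four single-parameter variables: 14 parameters, so 28 − 3 − 14 = 11.
- Five single-parameter variables, no school dummies: 28 − 3 − 5 = 20.
- No cluster covariates, for reference: 28 − 3 = 25.

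**4. Why the estimator matters.** Take total variance as 1. The variance of a year-group mean is 0.025 + 0.975/26 = 0.0625, of which 0.0375 is pupil-level. ML divides the between-group residual sum of squares by 28. With 11 df its expected value is (11/28) × 0.0625 = 0.0246, below 0.0375, so the year-group variance is set to zero when a chi-square on 11 df falls below 28 × 0.0375 / 0.0625 = 16.8. That happens with probability about 0.89 (0.60 on 16 df, 0.33 on 20 df). Under REML the corresponding figures are 0.17, 0.11 and 0.08.

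When ML does return zero, the pooled variance is about (11 × 0.0625 × 26 + 700 × 0.975) / 728 / 26 = 0.0370. The z statistic is then too large by √(0.0625/0.0370) = 1.30, and 1.96/1.30 = 1.51 has a two-sided tail of about 13%.

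**5. Simulated familywise error.** Null trials: two-level model, 28 equal year groups of 26, random cluster covariates, 10 designs × 4,000 trials per setting. Results at ICC 0.025:

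| Cluster covariate parameters (df) | REML, z | ML, z | REML, t | ML, t |
|---|---|---|---|---|
| 14 (11) | 6.7% | 14.4% | 3.6% | 8.6% |
| 9 (16) | 6.6% | 13.1% | 4.2% | 9.1% |
| 5 (20) | 6.4% | 11.0% | 4.6% | 8.2% |
| 0 (25) | 6.4% | 7.8% | 4.9% | 6.2% |

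Here z means the Dunnett value 2.212, and t means the multivariate-t Dunnett value on the residual df (2.535 on 11, 2.380 on 20). Repeat simulation gave 6.5-7.0% for REML and 8-15% for ML.

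**6. Sensitivity to the ICC** (14 parameters, z-based):
- ICC 0.005: REML 4.6%, ML 7.0%
- ICC 0.05: REML 8.1%, ML 22.6%

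**The case against.** The strongest objection is that the premise is not in the document. The article names a model class and a package. It does not say ML or REML, z or t. Dunnett's procedure in its standard form uses a multivariate t. Estimator, degrees of freedom and covariate coding are commonly left to an analysis plan, which is not shown here, so their absence is not an error in itself. This stands, and it limits the point to a conditional one.

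Three further objections also stand in part:
- **Fourteen parameters is an upper bound.** School may enter as a random level. Available year groups, PSHE frequency or timetabling may be school-level, in which case they cost nothing beyond the school dummies. However, z-based tests exceed 5% at ICC 0.025 under every coding tried, including none; the parameter count determines by how much.
- **The ICC is weak.** It comes from one pilot school, about 711/203 = 3.5 year groups. It is not said to apply to the high-risk subgroup or after baseline adjustment.
- **The simulation is simplified.** It uses equal cluster sizes and synthetic covariates, with no baseline SMFQ.

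A reader might infer that the trial's error rate simply is 7-15%, or that the reported intervals will be too narrow. The article does not support that, because nothing in it commits the analysts to large-sample tests. The power figures matching normal quantiles concerns the design stage and is not proof of how the primary test will be done. Nor is the year-group random effect at risk of being dropped: the article guarantees at least that level.

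**Conclusion.** The concern holds in conditional form. What the article fixes is a covariate-heavy random-effects model on 28 clusters, and nothing in it ties the two primary comparisons or the Dunnett adjustment to the roughly 11-20 degrees of freedom that remain. If z-based Dunnett values are used, familywise error at ICC 0.025 would be about 6.5-7% with REML, a modest excess, and about 8-15% with ML. The top of the ML range needs many fixed cluster-level parameters as well. REML shows no excess near ICC 0.005, and inflation under both estimators grows with the ICC. Guaranteeing a year-group level does not remove the problem, because ML can keep the level and still estimate its variance at zero.

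Should-fix, not must-fix: the unseen analysis plan may already deal with it, and under REML the excess is small.

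**What to change.** In the Statistical analysis section, or in the analysis plan if it is silent:

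1. State that the model is fitted by REML (RIGLS in MLwiN). A t reference alone is not enough: ML with a t-based Dunnett value still gives about 6-9% at ICC 0.025.
2. Take both contrasts, the simultaneous 95% intervals and the Dunnett p-values from a multivariate t on 28 minus the arm and cluster-level parameters. Alternatively, use Kenward-Roger or Satterthwaite in software that offers it.
3. State how the six balancing variables are coded, so that the degrees of freedom are fixed in advance.
4. If the balanced subset of allocation sequences was kept, which the article does not say, run a randomisation test over it as a sensitivity check.

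**Cost.** This changes analysis wording only, and according to Study Status the 12-month follow-up was still under way. Intervals widen by about 9% on 16 df (2.42/2.212) and 15% on 11 df (2.535/2.212), and slightly less on 20 df (2.380/2.212, about 8%). Tests become somewhat conservative at low ICC (2.1% familywise at ICC 0.005 on 11 df). The detectable effect with 28 year groups rises from 0.353 SD to (2.535 + 0.876) × 0.1157 = 0.395 SD, or 0.395 × 4.9 = 1.9 points. That is still inside the planned range, before any loss from correlation between arm and covariates.

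### The primary ANCOVA uses one of the two SMFQ scores that every analysed pupil already has; adding the screening score would give a small precision gain at almost no cost

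*Protocol article*

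**What the plan says.** The Statistical analysis section of the protocol article specifies an analysis of covariance of the 12-month SMFQ, fitted as a random-effects linear regression, and fixes its covariates: "Covariates in the model will comprise SMFQ baseline score and the six variables used to balance the trial arms in the allocation procedure". Under Randomisation, those six variables are school, available year groups, number of students, number of classes, PSHE frequency and PSHE timetabling.

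The primary analysis is confined to high-risk pupils, identified "based on their screening and baseline SMFQ scores (≥ 5 on both occasions". Participant Classification explains the double measurement: "MFQ scores are collected on two separate occasions approximately two weeks apart", so that a passing dip in mood does not by itself put a pupil in the high-risk group. The Design section gives the schedule as "initial screening, baseline (2 weeks after screening), 6 months and 12 months".

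The Power calculation section mentions no covariate adjustment.

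**The concern.** Two SMFQ scores, two weeks apart, exist for each pupil in the primary analysis, and the model uses only the second. The six balancing variables describe schools or year groups. Baseline SMFQ is therefore the only listed covariate that distinguishes pupils within the same year group, and selection at 5 or above truncates its range. A single score is also a noisy measure of a pupil's persistent level, which is why risk classification uses two occasions.

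If the screening score predicts the 12-month score beyond what baseline does, leaving it out makes the residual variance, and so the confidence interval, slightly larger than necessary. The 28 year groups are already randomised, so precision can no longer be gained by adding clusters. At stake is precision alone, not validity.

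**Working it through.** **Inputs from the Power calculation section.** The pilot "provided estimates of ICC (0.025), mean year group size (n = 203") and an "SMFQ standard deviation (4.9"). Consent 80%, retention 80%, high-risk share 20%; 80% power, 5% two-sided alpha, 20-27 year groups. An equal split of year groups over three arms is assumed, because the article does not state the ratio.

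**Step 1: reproduce the plan's figure.**
- Analysed pupils per year group: m = 203 × 0.8 × 0.8 × 0.2 = 25.98.
- Design effect: 1 + (25.98 − 1) × 0.025 = 1.625.
- Detectable effect: d = (z for alpha + z for power) × √(2 / n_eff), with n_eff = (k/3) × m / 1.625.
- With 5% divided over the two comparisons (2.5% each): 2.241 + 0.842 = 3.083.
- k = 27: n_eff = 9 × 25.98 / 1.625 = 143.9, so d = 3.083 × √(2/143.9) = 0.363.
- k = 20: n_eff = 6.667 × 25.98 / 1.625 = 106.6, so d = 0.422.

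A large-sample Dunnett critical value of 2.212 gives 0.360 and 0.418. Either way this matches the statement that "effect sizes in the range of 0.36-0.42 SDs are detectable". An unadjusted 5% per comparison gives 0.330 and 0.384, which does not match.

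**Step 2: where the variance lies.** Per year group and in SD² units, the variance of the mean is 0.025 + 0.975/25.98 = 0.0250 + 0.0375 = 0.0625. The between-year-group share is 0.0250/0.0625 = 40%. A pupil-level covariate is taken to act only on the other 60%.

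**Step 3: gain from the second score.** The article gives no correlation between SMFQ occasions. Assumptions, for unselected pupils: screening-baseline correlation 0.6-0.8; each score correlated 0.3-0.6 with the 12-month SMFQ, equally for both. A skewed 0-26 score with mean 4.8 and SD 4.9 was simulated and restricted to pupils scoring 5 or more on both occasions. R² is the share of 12-month variance explained in that group. Detectable effects are for 27 year groups.

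| Screening-baseline r | r with 12 months | R², baseline only | R², both scores | Cut in residual variance | Detectable effect (SD) | Power, from 80% |
|---|---|---|---|---|---|---|
| 0.8 | 0.3 | 0.023 | 0.030 | 0.7% | 0.361 → 0.360 | 80.2% |
| 0.7 | 0.5 | 0.078 | 0.109 | 3.4% | 0.355 → 0.351 | 80.9% |
| 0.6 | 0.6 | 0.130 | 0.197 | 7.7% | 0.349 → 0.341 | 81.9% |

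Middle row in full:
- Residual variance ratio: (1 − 0.109)/(1 − 0.078) = 0.966, a 3.4% cut.
- Variance per year-group mean: 0.025 + 0.975 × 0.922/25.98 = 0.0596 with baseline only; 0.025 + 0.975 × 0.891/25.98 = 0.0584 with both scores.
- Detectable effect: 3.083 × √(2 × 0.0596/9) = 0.355, against 3.083 × √(2 × 0.0584/9) = 0.351.
- Power for an effect that has 80% under the baseline-only model: Φ(3.083 × √(0.0596/0.0584) − 2.241) ≈ 80.9%.
- The confidence interval narrows by about 1%.

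In the most favourable row the detectable effect falls by about 0.04 SMFQ points (0.349 × 4.9 = 1.71; 0.341 × 4.9 = 1.67), against a stated target of around 2 points.

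**Step 4: sensitivity.** The skewed model puts 25-29% of pupils in the high-risk group, above the planned 20%. A normal model with the cut-off set to give exactly 20% yields variance cuts of 0.6-7% and power of 80.2-81.7%. If the year-group variance shrank in the same proportion as the pupil-level variance, power would reach about 83% at most.

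**The case against.** The strongest reply is that nothing here is wrong. Adjusting for the baseline value of the outcome and for every balancing variable is conventional, pre-specified and valid. It gives no bias, no invalid test and no ambiguity. The gain is slight, and its size rests wholly on correlations that the article does not report. All of this stands, and it sets the severity. It does not remove the point, because the covariate list is closed, the score is already collected, and the gain is positive throughout the assumed range.

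Four stronger readings are tempting, and the article does not support them.
- **That baseline SMFQ is the only adjustment.** It is the only SMFQ score adjusted for. The six balancing variables are also in the model, and they address differences between schools and year groups.
- **That the protocol itself distrusts baseline SMFQ as a covariate.** Participant Classification uses two scores to handle transient mood when assigning risk status. It makes no statement about covariate quality.
- **That chance imbalance in the screening score threatens the comparison.** Such imbalance does not bias a randomised comparison, baseline SMFQ absorbs part of it, and no imbalance is shown.
- **That the same change is free in every SMFQ analysis.** The subgroup analysis by baseline SMFQ includes pupils scoring below 5. They are outside the high-risk group, so nothing guarantees that they have a screening score.

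**Conclusion.** The point holds as a low-severity efficiency suggestion for the primary high-risk model. The omission of the screening SMFQ, and its availability for every pupil in that analysis, are certain from the text. The size is not. Under the assumed correlations, pupil-level residual variance falls by about 0.7-8% and power rises by about 0.2-2 percentage points. The gain would be smaller if the screening score predicted the 12-month score less well than baseline does.

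A reader might infer that the trial is underpowered or its primary analysis flawed. Neither follows: the detectable effect of 0.36-0.42 SD is reproduced without any covariate adjustment, and no stated figure needs to change.

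**What to change.** Before outcomes are analysed, add the screening SMFQ to the covariates of the primary high-risk model. Entering the mean of the screening and baseline scores together with their difference is an equivalent parameterisation. State the choice in advance so that it cannot look data-driven later.

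The cost is one sentence and one degree of freedom. No new data are needed and no pupil leaves the primary analysis, since both scores are required for high-risk status. Do not carry the covariate into SMFQ analyses that include pupils below 5 at baseline unless the plan also says how missing screening scores will be handled.
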